### Intervention group

After baseline data collection, teachers in the intervention group will attend a 1-hour face-to-face professional learning session. This session will cover the following topics: defining and understanding the benefits of physical activity, defining and understanding the impact of sedentary behaviour, information about *TransformUs Secondary* and explaining the six programme components, practical demonstrations of how to plan for and deliver active breaks and active lessons in their teaching and how to navigate and obtain the programme resources from the website, with opportunities to experience and deliver active breaks and lessons in an environment that fosters meaningful activity. Teachers will be encouraged to register on the *TransformUs* Website, plan for and use the programme resources in all their lessons, encourage their students to participate as champions/leaders for activities inside and outside the classroom, visit the website regularly and request assistance from the research team when needed via *TransformUs Secondary*’s email or phone. In addition, schools will receive $A2000 to assist with programme implementation. Teachers and school leaders will be asked to decide how to use the funds to support the delivery of prioritised strategies (eg, active equipment, line markings, height adjustable desks and classroom signage).

### Waitlist control group

Schools assigned to the waitlist control group will be asked to continue their usual lesson delivery and will receive professional learning, access to the online programme resources and $A2000 implementation funds at the completion of the postintervention data collection.

### Measures

All assessments will occur at two time points. Baseline assessments will be conducted before the beginning of the trial and repeated after 6 months or 2–3 school terms of intervention delivery. The measures will be taken by trained research staff. Student-level outcomes will be used to determine the effectiveness of the programme on adolescents’ physical activity and sedentary time (primary outcomes) and on sleep duration and quality, class engagement, well-being, students’ physical activity during morning recess and lunch breaks, on-task behaviour in class and sitting time (secondary outcomes). Students with informed consent will complete a brief online survey, approximately 10–15 min in duration, at school. Following the survey, the research team will distribute and provide instructions for the use of the activity device to students with consent in a room assigned by the school. Meanwhile, teachers will receive a survey link via their work email, allowing them to complete the assessment at their convenience. To ensure timely participation, students will receive SMS reminders to wear the devices, and teacher will receive a reminder to complete the survey.

### Student-level outcomes

#### Device-assessed physical activity, sedentary time and sleep

Participants will wear an ActiGraph GT9X accelerometer (ActiGraph LLC, Pensacola, Florida, USA) on their non-dominant wrist for 24 hours a day for eight consecutive days at both measurement points. This device measures the acceleration and deceleration of human movement. Acceleration data can be used to identify the intensity of a given movement as well as its underlying temporal pattern (ie, frequency, duration) over defined epoch durations (eg, during recess and lunch periods).^38^ This device has demonstrated validity and reliability in adolescents.^39^ Data will be reduced using evidenced-based, best-practice procedures at the time of analysis (eg, open-source package General Goodness of Fit (GGIR) in R software) to obtain the time (during school, recess and lunch, and waking hours) spent sedentary and in MVPA on an average school day and average weekday and weekend days (primary outcomes) and light, moderate and vigorous physical activity (during school, recess and lunch, average school day and average day (weekday and weekends)) and average sleep duration (secondary outcomes).

#### Device-assessed sitting time

Students can also opt to wear an activPAL3 inclinometer (PAL Technologies, Glasgow, UK) on the front of their right thigh (at the mid-point), attached via an elastic belt during waking hours, for 8 days at each of the measurement points. This device (sampling at 10 Hz) detects limb position and is a valid and reliable device for measuring sitting, standing and stepping time in children and adolescents.^40^ Average minutes (during school, recess and lunch, average school day and average day (weekday and weekend days)), spent sitting, in continuous sitting bouts, standing, stepping and the number of transitions from sitting will be computed from activPAL data using ProcessingPAL.^41^

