### Data analysis

Analysis of the primary and secondary outcomes will be performed using Stata 18 for Windows (StataCorp LP) and RStudio V.1.4.453 (R V.3.6.3; R Foundation for Statistical Computing, Vienna, Austria).

Descriptive analyses will be employed to depict the quantitative data collected for all variables of interest, including students’ demographic characteristics, physical activity, sedentary behaviour, sleep, well-being, class engagement, school environment and intervention implementation measures (eg, school audit data) at each time point. Data will be examined for missing values, outliers and distributional assumptions. Teachers’ demographic characteristics and survey responses from both intervention and control groups will be described.

For the primary outcomes, random intercept linear mixed models will be used (where the unit of the analysis (students) will be nested within year levels within schools) to examine the intervention effects on primary (physical activity and sedentary time) and secondary (sleep and well-being, class and school engagement, reducing sitting time, increasing light, moderate and vigorous physical activity, self-report physical activity/sedentary behaviours, observed physical activity during recess and lunch time and engagement with the intervention strategies) outcomes among adolescents. All models will be adjusted for measured confounders age, gender, baseline values, socioeducational advantage strata (high vs low ICSEA) and school type (Government, Independent, Catholic).

The programme’s reach, adoption, implementation, and organisational-level maintenance aspects will be presented descriptively. Linear or logistic regression models will be used to compare differences between intervention and control groups in teacher perceptions of school readiness, climate, and environment, as well as teacher practices, competence levels, and implementation barriers, adjusting for baseline values as covariates. The school grounds audit data will be analysed using descriptive statistics to characterise the physical environment of intervention and control schools and interactions with the intervention effects will be examined to determine if there was a potential moderator effect by school environment.

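### Whole-day activPAL minutes depend on how long the belt is worn, and the covariate list stated for all models has no wear term

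*Protocol article*

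**What the plan says.** **Sitting device.** Under Device-assessed sitting time, the opt-in activPAL is "attached via an elastic belt during waking hours, for 8 days at each of the measurement points". The outcomes are average minutes, for the school day and its breaks and also for whole days: time "spent sitting, in continuous sitting bouts, standing, stepping and the number of transitions from sitting will be computed from activPAL data using ProcessingPAL".

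**Wrist device.** Under Device-assessed physical activity, sedentary time and sleep, the ActiGraph is worn "on their non-dominant wrist for 24 hours a day for eight consecutive days at both measurement points". On processing, the plan says "Data will be reduced using evidenced-based, best-practice procedures at the time of analysis", with GGIR as an example. The primary outcomes are "time (during school, recess and lunch, and waking hours) spent sedentary and in MVPA".

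**Model.** The effectiveness trial's Data analysis section states: "All models will be adjusted for measured confounders age, gender, baseline values, socioeducational advantage strata (high vs low ICSEA) and school type". The same section says "Data will be examined for missing values, outliers and distributional assumptions".

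**Context.** The trial is open (Blinding). Schools are placed in an arm on practical grounds of availability and timing, not at random (Effectiveness trial). Students get text reminders to wear the devices (Measures).

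The article does not express any device outcome relative to worn time, and no wear term appears in a model.

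**The concern.** A belt that the student puts on in the morning and takes off later records sitting only while it is on. A whole-day total is therefore the share of worn time spent sitting multiplied by the minutes worn. Two students who behave identically get different totals if one wears the belt longer.

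This matters in two ways. First, wear variation between students adds variance to every whole-day total, even when the arms wear the belt equally. Second, if average wear differs between arms at follow-up, the difference enters the estimated intervention effect. Neither randomisation nor blinding guards against that here, and control schools are still waiting for the programme when follow-up is measured. The baseline value in the model corrects only for what was already different at baseline.

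The covariate list is a stated choice covering all models. A rule for what counts as a valid day, wherever it is written, would decide which days enter the average. It would not equalise worn minutes among the days that pass.

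**Working it through.** **The plan's own figures.** The plan gives no wear time, standard deviation or detectable difference for sitting or sedentary time, so there is no figure on this point to reproduce. Its one power statement concerns MVPA and does not bear on the question.

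**Inputs**
- Sedentary share of waking time, p: more than two-thirds (Introduction). I use 2/3.
- Sitting share of school time: more than three-quarters (Introduction), used as a second value.
- MVPA share of worn time: not in the documents; assumed 3% to 8%.
- Between-arm difference in wear at follow-up, d: not in the documents; assumed 10, 30 and 60 min/day.

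**Shift in recorded minutes with no change in behaviour.** Let both arms have share p, with wear W in one arm and W − d in the other. Then

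difference in recorded minutes = p(W − d) − pW = −p·d.

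| Outcome and share | d = 10 | d = 30 | d = 60 |
|---|---|---|---|
| Sitting or sedentary, 2/3 | 6.7 | 20 | 40 |
| Sitting, 3/4 | 7.5 | 22.5 | 45 |
| MVPA, 3% to 8% | 0.3–0.8 | 0.9–2.4 | 1.8–4.8 |

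At p = 2/3, standing and stepping together take the rest of the lost time: 10 − 6.7 = 3.3 min/day for d = 10. The sign depends on which arm wears the belt less. The calculation assumes that the unworn minutes have the same sitting share as the worn ones. For sitting, the limits at d = 10 are 0 min/day (none of the lost time was sitting) and 10 min/day (all of it was).

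**Why baseline adjustment does not help.** If wear is equal at baseline, the arms have equal baseline minutes on average. The adjustment subtracts slope × 0 = 0, and the shift of −p·d stays.

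**Why a proportion does.** Take W = 840 min (assumed), d = 30 and p = 2/3. Totals are 840 × 2/3 = 560 and 810 × 2/3 = 540, an apparent difference of 20 min. As a share of worn time both are 2/3, which rescales to 560 min on a common 840-min day, a difference of 0.

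**Simulation check.** No behaviour change; 10 schools of 48 students; wear mean 840 and SD 60 min/day, sitting share mean 2/3 and SD 0.05 (all assumed except the share of 2/3 and the school sizes); 400 replications; ordinary regression without clustering.

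| Wear gap (min/day) | Baseline minutes only | Plus wear at both visits |
|---|---|---|
| 0 | 0.2 | −0.1 |
| 15 | −10.1 | −0.1 |
| 30 | −20.5 | −0.1 |
| 60 | −40.1 | 0.2 |

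**Equal wear in both arms.** With the same assumed SD of 60 min/day, wear variation alone contributes an SD of about 2/3 × 60 = 40 min/day to whole-day totals.

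**The case against.** The strongest reply is that this is processing detail. The wrist data are to be reduced by best-practice methods, the activPAL data go through ProcessingPAL, and missing values will be examined. Non-wear and valid-day rules belong there, and a condensed article may leave them to a fuller document. This stands as far as it goes: the lack of a printed non-wear rule is no fault, and it would be wrong to say that unprocessed minutes are analysed. It does not answer the narrower point. The sitting outcomes are fixed as minutes from a waking-hours belt, and the covariate list is fixed for all models.

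Several stronger readings are tempting but are not supported:
- **That both primary outcomes share the defect.** The waking-hours belt is an optional device for a secondary outcome. The primary device is worn day and night, so non-wear there is a matter of compliance and may be dealt with in processing. MVPA moves little at any plausible share.
- **That every sitting outcome is exposed.** Putting the belt on in the morning and taking it off at night hardly touches the timetabled school, recess and lunch windows.
- **That the bias favours the intervention.** Open allocation could make intervention students more compliant or less. Lower wear in that arm would make sitting look better and MVPA slightly worse; higher wear would do the reverse.
- **That 6.7 min/day of sitting matches the 7 min/day in the power statement.** That figure is for MVPA, a different outcome with a different spread.

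A further objection concerns the remedy. Worn waking time at follow-up is measured after allocation, and sleep is itself an outcome. Conditioning on waking time could therefore remove part of a real effect. This is a fair caution, and it is why unadjusted minutes should still be reported.

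**Conclusion.** The point holds for whole-day activPAL sitting, standing and stepping. As written, these totals depend on worn time, and nothing in the stated model corrects for it. The size is about 6.7 min/day of recorded sitting per 10 min/day of wear difference, in either direction. This rests on the Introduction's two-thirds share and on unworn time resembling worn time. Any actual wear gap between arms is an assumption; the documents neither give one nor show that one will arise.

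For whole-day sedentary time on the wrist device, the same arithmetic applies only if processing leaves non-wear uncorrected, which cannot be judged from the article. The documents do not support extending the point to MVPA or to the fixed windows within the school day. It is a worthwhile and inexpensive improvement, not a flaw that undermines the trial.

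**What to change.** In Device-assessed sitting time and in the effectiveness trial's Data analysis section:

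1. Analyse whole-day sitting, standing and stepping as a percentage of valid worn waking time, rescaled to a common day length. Alternatively, add valid wear minutes at both time points to those models. Choose one in advance.
2. Treat whole-day sedentary time from the wrist device the same way, unless the processing already corrects for non-wear; if it does, say so.
3. Report worn time by arm at baseline and follow-up for both devices.
4. Keep unadjusted minutes as a sensitivity analysis, since waking time could itself change through sleep.

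MVPA and the school, recess and lunch outcomes can stay as they are. For activPAL wearers, the 24-hour wrist record can supply the waking window.

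The cost is a few sentences and some extra processing, with no new data and no change to the sample size. The downside is that the effect is expressed per standardised worn day and not as total minutes.

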#### Self-reported sociodemographic characteristics, physical activity, sleep, wellbeing and class engagement

Students will self-report their *sociodemographic characteristics*, including age, gender, year level, country in which they were born and main language spoken at home. The Youth Activity Profile will be self-administered to capture *school-related physical activity and sedentary behaviour*. This 7-day recall instrument is designed to facilitate physical activity assessment in youth and has been validated for school-based assessments.^42^ The 15-item questionnaire comprised three sections (school day, out-of-school and sedentary behaviour), with five questions per section. During context-specific time segments, participants are asked to recall their physical activity and sedentary behaviour over the past 7 days^42^ (online supplemental file 4E). The *Adolescent Sleep Wake Scale* (ASWS) is a brief questionnaire, consisting of 20 items, that has been validated to assess overall sleep quality and insomnia symptoms in adolescents (ages 12–18).^43^ The ASWS includes five subscales that measure different aspects of sleep behaviour, including Going to Bed, Falling Asleep, Maintaining Sleep, Reinitiating Sleep and Return to Wakefulness. Scores for the total scale and each subscale are calculated as the average of the respondent’s answers to all items, rated on a scale from 1 (‘Always’) to 6 (‘Never’). Higher scores on the ASWS indicate better sleep quality. In addition, several questions from the self-report Child and Adolescent Sleep Checklist (CASC) will be used to measure sleep duration.^44^ This included questions on total sleep time, bedtime and wake time on weekdays and weekends over the past week. The *Engagement, Perseverance, Optimism, Connectedness, and Happiness* questionnaire is designed to assess positive psychological functioning and emotions in adolescents and encompasses five positive psychological traits: engagement, perseverance, optimism, connectedness and happiness.^45^ Students will be asked to rate 10 items on a 5-point scale, ranging from ‘almost never’ to ‘almost always’ and 10 items on a scale ranging from ‘not at all like me’ to very much like me’. Scores are then calculated for each of the five domains, providing an indication of an individual’s level of positive psychological functioning and feelings.^45^ Higher scores indicate more engagement, perseverance, optimism, connectedness, and happiness (online supplemental file 4E). The behavioural and emotional/motivational aspects of students’ *classroom engagement* will be captured using the Engagement vs Disaffection with Learning survey.^46^ Respondents use a 4-point Likert-type scale ranging from 1 (not at all true) to 4 (very true). The tool consists of four dimensions and a total of 20 items hereafter organised to assess behavioural engagement, behavioural disaffection, emotional engagement and emotional disaffection at school. Higher scores on each dimension indicate more engagement or disaffection (online supplemental file 4E).

#### Students’ on-task behaviour

*Students’ on-task behaviour* will be assessed with direct observations, using momentary sampling with 15-s observation intervals. This approach is aligned with what was adopted in previous research^47^ and involves at least one researcher to be in the classroom and routinely observing students (1:6 observer/student ratio) during a classroom lesson. The observer will look at a target consented student for 5 s and use the remaining 10 s to record the momentary-observed behaviour and some contextual information (ie, the student’s movement behaviour and information on the task being conducted at the time). The same target students will be observed for four intervals (ie, 1 min) before moving to the next student. In a 30-min observation session, each student will be observed 20 times. Observed students’ behaviours will be classified as follows: focused on-task (the student is focused on the task assigned by the teacher, eg, reading, writing, asking/answering questions, active in a purposeful way that aligns with learning intentions), passive off-task (the student is not focusing on the assigned task and shows passive disengagement, eg, not focused, daydreaming, staring, drinking water), disruptive off-task (eg, the student is not focusing on the assigned task and shows a disruptive behaviour; not focused walking around, playing with irrelevant objects, fidgeting), absent (eg, the student left the classroom). Contextual information relating to students’ movement behaviours will be classified as follows: sitting, standing, walking slow, walking fast and moving fast (eg, jumping). Information on the setting/task will be coded as follows: independent task, paired task, group task, teacher-led activity, test and other. To ensure consistency in the observation and data collection processes, an online observation tool to record students’ behaviour was developed in the Qualtrics survey by the research team (online supplemental file 4F).

#### Student attendance

Overall student attendance data will be collected for each participating school at baseline and 6 months. The percentage of actual full-time equivalent student days attended as a percentage of the total number of possible student days attended over the (reporting) period will be collected from the Australian Curriculum, Assessment and Reporting Authority website (https://www.acara.edu.au/contact-us/acara-data-access).

#### Observed physical activity during recess and lunch

Students’ physical activity during recess and lunch will be assessed using the System for Observing Play and Leisure Activity in Youth (SOPLAY) at baseline and follow-up. SOPLAY is a validated tool for directly observing physical activity and associated environmental characteristics in free-play settings.^48^ SOPLAY provides objective data on the number of participants and their physical activity levels during play and leisure opportunities in targeted areas. The research staff will define the target areas. Separate scans are made for males and females, and simultaneous entries for contextual characteristics of areas including their accessibility, usability, and whether supervision, organised activities and equipment are provided. A map of the zones and SOPLAY data collection sheets will be provided to each research assistant. Observations will begin 5 min into recess and 10 min into lunch and occur every 5 min. Research assistants will rotate clockwise around the zones, with each group starting in a different zone. Observations will end 5 min before the end of recess/lunch. All observations will be recorded on the SOPLAY data collection sheet. The predominant type of activity engaged in by area users will also be recorded (eg, basketball, dance) (online supplemental file 4G).

#### Engagement with the intervention strategies

Students’ experience/access to intervention strategies will be assessed with seven survey questions developed by the research team. The questions will determine if their school has organised (eg, by teachers/schools or students) physical activities at lunch/recess, outdoor and classroom environment that promotes movement, teachers who deliver active lessons/breaks and teachers who give active homework. Respondents use a 6-point Likert-type scale ranging from 1 (doesn't have) to 6 (strongly agree) (online supplemental file 4E).

### Teacher-level outcomes

Self-reported sociodemographic data, physical activity and perceptions of school readiness, climate and environment; teacher practices, competence levels and implementation barriers and teachers’ perceptions of the programme reach, effectiveness, adoption, implementation and maintenance will be assessed using the same survey described for the implementation trial section and detailed in the online supplemental file 4D).

